## Abstract

**Background:**

Brainstem infarction is a clinically important subtype of posterior circulation infarction and is often associated with disability and poor functional recovery. Disease-specific therapeutic strategies remain limited, and rehabilitation-oriented evidence specifically targeting functional recovery in this population remains insufficient. Acupuncture has been studied and applied as an adjunctive approach for stroke rehabilitation in multiple regions; however, high-quality evidence for its use in brainstem infarction remains scarce. This trial primarily aims to evaluate whether adjunctive Shallow Acupuncture improves activities of daily living in patients with brainstem infarction; as an exploratory objective, it will examine associated neural changes assessed by resting-state functional magnetic resonance imaging (rs-fMRI) and diffusion tensor imaging (DTI).

**Methods and analysis:**

This is a single-center, randomized, assessor- and statistician-blinded, pragmatic add-on controlled trial. A total of 62 patients with brainstem infarction will be randomly assigned in a 1:1 ratio to a conventional acupuncture group or an adjunctive Shallow Acupuncture group. In keeping with routine inpatient practice in the acupuncture department, both groups will receive standard medical management, routine rehabilitation, and conventional acupuncture, while the adjunctive Shallow Acupuncture group will additionally receive Shallow Acupuncture once daily for 14 consecutive days. The primary clinical outcome will be activities of daily living, assessed by the Barthel Index. Secondary clinical outcomes will include the National Institutes of Health Stroke Scale and the modified Rankin Scale. Exploratory indicators will include measures derived from rs-fMRI and DTI. rs-fMRI analyses will focus primarily on resting-state functional connectivity, whereas DTI analyses will focus primarily on fractional anisotropy; mean diffusivity will be examined as an exploratory diffusion metric. Clinical outcomes will be assessed at baseline, post-treatment, and 1-month follow-up, and neuroimaging assessments will be performed at baseline and post-treatment.

**Ethics and dissemination:**

This study has been approved by the Ethics Committee of Guangdong Provincial Hospital of Chinese Medicine (approval numbers: YE2024-202-01 and YE2024-203-01). The findings will be disseminated through peer-reviewed publications and academic conferences.

**Clinical trial registration:**

https://itmctr.ccebtcm.org.cn/zh/index.html. Identifier, ITMCTR2024000456.

## Introduction

Brainstem infarction, a subtype of ischemic stroke, refers to ischemic necrosis of the midbrain, pons, or medulla oblongata caused by stenosis or occlusion of the vertebrobasilar artery and its branches, accounting for approximately 10–15% of all ischemic stroke (1). Located at the base of the brain, the brainstem serves as a major pathway for motor and sensory tracts, harbors nuclei and fibers of ten cranial nerves, and regulates core functions such as cardiac and respiratory activity, consciousness, and sleep–wake cycles (2). Because of its structural complexity and critical physiological roles, even small lesions in this region can provoke severe and heterogeneous clinical manifestations (3). Compared with ischemic strokes in other locations, brainstem infarction is characterized by a more abrupt onset and a more severe clinical course (4) and represents a significant contributor to global stroke-related morbidity and mortality (1). However, despite its clinical importance and generally poor prognosis, research specifically focusing on brainstem infarction remains limited, and disease-specific therapeutic strategies are still lacking (5).

Current management of brainstem infarction largely follows general treatment principles for ischemic stroke, including acute reperfusion therapy, neurosurgical procedures, and pharmacological treatment (5). Although acute reperfusion therapies remain important, their applicability is constrained by narrow therapeutic time windows, restricted indications, and uncertain benefit in some patients (6–8). Neurosurgical intervention is generally reserved for selected life-threatening conditions rather than routine management (5), whereas pharmacological treatment mainly focuses on secondary prevention and provides limited direct benefit for functional recovery. Despite standard acute and medical management, many patients with brainstem infarction continue to experience disabling deficits and require rehabilitation-oriented management.

Current stroke rehabilitation strategies are typically individualized according to functional deficits and rehabilitation needs rather than determined solely by infarct location (9). As a result, patients with brainstem infarction are often managed within broader stroke rehabilitation frameworks. However, lesions involving the midbrain, pons, or medulla may result in heterogeneous and disabling functional deficits, including dysphagia, dysarthria, vertigo or dizziness, impaired balance, ataxia, limb weakness, and other related dysfunctions (1). In addition, posterior circulation infarction, including brainstem infarction, remains relatively under-researched compared with anterior circulation stroke (5). Therefore, high-quality rehabilitation-oriented evidence specifically targeting functional recovery after brainstem infarction remains limited. Accordingly, there remains a clear need to explore adjunctive strategies that may promote functional recovery after brainstem infarction.

Acupuncture has been investigated as an adjunctive approach for stroke rehabilitation in studies from multiple regions (10). In China, acupuncture is also recommended in the Chinese Guidelines for the Diagnosis and Treatment of Acute Ischemic Stroke 2023 as an adjunctive therapy for acute ischemic stroke (Class IIb recommendation, Level B evidence) (11). In routine clinical practice in Chinese tertiary hospitals of traditional Chinese medicine, conventional acupuncture is commonly incorporated into integrative rehabilitation for stroke. Although previous studies suggest that acupuncture may improve neurological symptoms after cerebral infarction, high-quality evidence specifically targeting posterior circulation infarction, particularly brainstem infarction, remains scarce (12–14).

In this study, we employ Shallow Acupuncture, a superficial needling technique in which the needle is inserted at a small angle and limited depth into the subcutaneous tissue or superficial muscle layer (15). Unlike conventional acupoint-based acupuncture, this technique emphasizes the identification and stimulation of pathological response points (16). These points are defined here as clinically identifiable reactive areas on the body surface that may reflect altered sensitivity, tenderness, or local neurovascular reactivity. For patients with brainstem infarction, the pathological basis is closely related to ischemia within the vertebrobasilar arterial territory (1). Previous studies have suggested that acupuncture applied to cervico-occipital regions may be associated with changes in vertebrobasilar blood flow and functional connectivity (17, 18), providing a regional neurovascular and neuroimaging rationale for considering cervico-occipital region stimulation. In our preliminary clinical observations, pathological response points in patients with brainstem infarction frequently clustered in the temporal and occipital regions, and stimulation of these regions appeared to be associated with improvement in symptoms such as dizziness. This observation further informed the selection of the temporal and occipital regions in the present protocol. In addition, our previous randomized clinical study reported that Shallow Acupuncture improved dizziness-related outcomes in patients with posterior circulation ischemic vertigo, providing clinical evidence for the application of this technique in posterior circulation ischemia-related symptoms (19). Taken together, these observations provide a rationale for the design of a disease-oriented and lesion-directed Shallow Acupuncture protocol for brainstem infarction. However, because the current supporting evidence remains indirect, the present protocol is best regarded as hypothesis-generating and requires prospective evaluation. Rigorous randomized controlled evidence remains lacking regarding whether adjunctive Shallow Acupuncture confers additional clinical benefit in brainstem infarction and whether any such benefit is accompanied by measurable neural changes.

To investigate whether adjunctive Shallow Acupuncture is accompanied by treatment-related neural changes after brainstem infarction, rs-fMRI and DTI provide complementary approaches for evaluating brain network reorganization and white-matter microstructural changes. Blood oxygen level–dependent functional magnetic resonance imaging (BOLD-fMRI), which indirectly reflects neuronal activity by detecting blood oxygen–dependent signals, has become a key tool for investigating brain functional activity (20). Previous studies have shown that patients with brainstem infarction exhibit abnormalities in resting-state network connectivity, and that these changes may be associated with functional recovery (21–23). Diffusion tensor imaging (DTI), by quantifying the diffusion properties of water molecules, enables assessment of white matter tract integrity (24). Fractional anisotropy (FA), a commonly used DTI parameter, has been shown to decrease after brainstem infarction, particularly in the corticospinal tract (CST), and subsequent FA recovery may be associated with more favorable motor outcomes (25–27).

Together, rs-fMRI and DTI may help characterize brain network reorganization and white-matter microstructural changes after brainstem infarction, thereby providing a multimodal framework for exploring clinical–imaging associations in response to adjunctive intervention. Against this background, the present randomized controlled trial is designed to evaluate the adjunctive effectiveness of Shallow Acupuncture in patients with brainstem infarction within routine integrative inpatient care. We hypothesize that, compared with standard care plus conventional acupuncture alone, adjunctive Shallow Acupuncture will be associated with greater improvement in activities of daily living and may be accompanied by changes in resting-state functional connectivity and white-matter microstructural integrity as assessed by rs-fMRI and DTI.

## Methods and analysis

### Study design

This is a single-center, randomized, assessor- and statistician-blinded, pragmatic add-on trial, in which a predefined subgroup of participants will undergo rs-fMRI and DTI assessment. All study procedures adhere to the Standard Protocol Items: Recommendations for Interventional Trials (SPIRIT) guidelines. Figure 1 outlines the study flow, and Table 1 details the schedule of enrolment, interventions, and assessments.

**Figure 1 fig1:**
[figure not shown]
Flowchart of the randomized controlled trial. BI, Barthel Index; NIHSS, National Institutes of Health Stroke Scale; mRS, modified Rankin Scale; fMRI, functional magnetic resonance imaging; DTI, diffusion tensor imaging.

**Table 1 tab1:** Schedule of enrolment, interventions, and assessments.

	Study period				
	Screening/Enrolment	Baseline (Day 0)	Treatment period (Day 1–14)	Post-treatment (Day 14)	Follow-up (1 month post-treatment)
Eligibility assessment	**×**				
Informed consent	**×**				
Brain MRI confirmation of brainstem infarction	**×**				
Demographic and clinical characteristics		**×**			
Documentation of pathological response points		**×**	**×**		
Randomization		**×**			
Standard medical management			**×**		
Routine rehabilitation			**×**		
Conventional acupuncture (both groups)			**×**		
Shallow Acupuncture (adjunctive Shallow Acupuncture group)			**×**		
BI		**×**		**×**	**×**
NIHSS		**×**		**×**	**×**
mRS		**×**		**×**	**×**
fMRI and DTI (imaging subgroup only)		**×**		**×**	
Adverse event/safety monitoring			**×**	**×**	

BI, Barthel Index; NIHSS, National Institutes of Health Stroke Scale; mRS, modified Rankin Scale; fMRI, functional magnetic resonance imaging; DTI, diffusion tensor imaging.

The study protocol has been reviewed and approved by the Ethics Committee of Guangdong Provincial Hospital of Chinese Medicine (Ethics Reference No: YE2024-202-01, YE2024-203-01). The trial has also been registered in the International Traditional Chinese Medicine Clinical Trial Registry (ITMCTR; registration number: ITMCTR2024000456).

### Setting and recruitment

This trial will be conducted in the inpatient Acupuncture Department of The Second Affiliated Hospital of Guangzhou University of Chinese Medicine (Guangzhou, China) from August 2025 to November 2026. During this period, 62 patients with brainstem infarction and 20 healthy volunteers will be recruited. The healthy volunteers will serve as a neuroimaging comparison group for the assessment of brain network and white-matter changes associated with brainstem infarction. Healthy volunteers will not undergo randomization or intervention and will receive a single rs-fMRI and DTI assessment for neuroimaging comparison. Because the study recruits inpatients from the acupuncture department, conventional acupuncture is incorporated into routine integrative stroke care in this clinical setting. Accordingly, the present trial is designed to evaluate the adjunctive effectiveness of Shallow Acupuncture on top of standard care and conventional acupuncture under real-world inpatient conditions.

### Inclusion criteria

Patients meeting all of the following criteria will be included:

Diagnosis of ischemic stroke consistent with the Guidelines for Primary Care of Ischemic Stroke (2021) (28), and brain MRI confirming a single ischemic infarction involving the brainstem, with the lesion confined to one side and not crossing the midline.Men or women aged 50–80 years, with a first-ever stroke and a disease duration ≤ 6 months.NIHSS score ≥ 2, and the presence of at least one assessable brainstem-related neurological deficit, such as dysphagia, dysarthria, vertigo, balance impairment, or ataxia.Clinically stable, without disturbance of consciousness, and able to understand and cooperate with study procedures.Able and willing to provide written informed consent.Not currently participating in any other clinical study.Right-handed prior to stroke onset, as assessed by the Chinese version of the Edinburgh Handedness Inventory (29).

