### Randomization

A computer-generated randomization sequence will be created by an independent researcher who is not involved in participant recruitment, treatment delivery, outcome assessment, or statistical analysis. Participants will be randomly assigned in a 1:1 ratio to the conventional acupuncture group or the adjunctive Shallow Acupuncture group, with 31 patients in each group. The allocation sequence will be concealed in sequentially numbered, opaque, sealed envelopes. The envelopes will be kept by designated study personnel and opened in numerical order only after an eligible participant has been enrolled. Participants will then be assigned to the corresponding group according to the allocation indicated inside the envelope.

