### Outcome measures

At baseline, demographic and clinical characteristics will be collected for all participants, including age, sex, educational level, occupation, and disease duration. In addition, the types and spatial distribution of pathological response points in the temporal and occipital regions will be documented.

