### Clinical data analysis

All clinical statistical analyses will be performed by independent statisticians who are blinded to group allocation, using SPSS version 26.0 (IBM Corp., Armonk, NY, USA). The primary clinical analysis will focus on the between-group difference in BI change after treatment. Analyses of clinical outcomes will primarily follow the intention-to-treat principle, including all randomized participants according to their allocated group. A per-protocol analysis may also be conducted as a sensitivity analysis in participants who complete the assigned intervention. Missing data will be handled using appropriate statistical methods depending on the extent and pattern of missingness.

Continuous variables will be presented as mean ± standard deviation (SD) when normally distributed or as median with interquartile range (IQR) when non-normally distributed. Categorical variables will be summarized as frequencies and percentages. Between-group comparisons of continuous variables will be performed using the independent-samples t-test for normally distributed data or the Mann–Whitney U test otherwise. Within-group changes over time will be assessed using paired-samples t-tests or Wilcoxon signed-rank tests, as appropriate. For categorical or ordinal variables, the chi-square test, Fisher’s exact test, or rank-sum test will be used as appropriate. Clinically relevant concomitant medications and rehabilitation interventions will be summarized by group using descriptive statistics, with attention to the magnitude and clinical relevance of any between-group differences. If clinically meaningful imbalances in co-interventions are observed, these factors will be considered in the interpretation of the results, and exploratory sensitivity analyses or covariate-adjusted analyses may be performed as appropriate.

For repeated clinical assessments, changes over time and between-group differences will be further evaluated using repeated-measures analysis or an equivalent mixed-effects approach, where appropriate. The relationships between clinical outcome measures and imaging parameters will be assessed using Pearson or Spearman correlation analyses, depending on the distribution of the data. All statistical tests will be two-sided, and a *p*-value < 0.05 will be considered statistically significant.

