### Neuroimaging data analysis

Neuroimaging analyses will be conducted in the predefined imaging subgroup and will be considered secondary and exploratory. Given its potential influence on rs-fMRI and DTI measures, age will be considered as a covariate in exploratory neuroimaging analyses where appropriate. Resting-state fMRI data will be preprocessed using SPM12 (Wellcome Trust Centre for Neuroimaging, London, UK) running on the MATLAB platform. The preprocessing pipeline will include slice-timing correction, head-motion correction, spatial normalization to Montreal Neurological Institute (MNI) space, and spatial smoothing.

rs-fMRI analyses will focus primarily on resting-state functional connectivity (FC). Independent component analysis (ICA) will be performed using the Group ICA of fMRI Toolbox (GIFT). The analysis will include dimensionality reduction, ICA decomposition, and component back-reconstruction. The number of independent components will be estimated according to the minimum description length criterion, and the Infomax algorithm will be used for ICA decomposition. Component stability will be evaluated using ICASSO, and components with a stability index > 0.90 will be retained. Spatial maps will then be converted into z-score maps, and functionally meaningful resting-state networks will be identified by comparison with standard network templates.

DTI data will be processed using the FMRIB Software Library (FSL, Oxford, UK). Preprocessing will include eddy-current correction, head-motion correction, and registration to standard space. DTI analyses will focus primarily on fractional anisotropy (FA), with particular attention to the corticospinal tract (CST) and other major motor-related white matter pathways. Mean diffusivity (MD) will be examined as an exploratory diffusion metric. Group comparisons of diffusion indices will be performed using the Randomise tool in FSL, with permutation-based nonparametric testing and threshold-free cluster enhancement (TFCE) for multiple-comparison correction. For imaging analyses, results will be interpreted primarily as exploratory, and corrected *p*-values < 0.05 will be considered statistically significant.

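### Entry runs up to 6 months after stroke, yet the primary Barthel Index comparison adjusts for neither time since stroke nor baseline score: precision may be lost, not validity

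*Protocol article*

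**What the plan says.** All references are to the protocol article.

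- **Inclusion criteria:** "Men or women aged 50–80 years, with a first-ever stroke and a disease duration ≤ 6 months". No minimum time since onset is given, although patients must be clinically stable.
- **Outcome measures:** the baseline data are listed as "including age, sex, educational level, occupation, and disease duration", so time since stroke will be on file for every patient.
- **Randomization:** patients are "randomly assigned in a 1:1 ratio to the conventional acupuncture group or the adjunctive Shallow Acupuncture group, with 31 patients in each group". No stratification factor is named.
- **Clinical data analysis:** "The primary clinical analysis will focus on the between-group difference in BI change after treatment". The tests are then named: "Between-group comparisons of continuous variables will be performed using the independent-samples t-test for normally distributed data or the Mann–Whitney U test otherwise". Repeated assessments are "further evaluated using repeated-measures analysis or an equivalent mixed-effects approach, where appropriate", with no covariate listed. Adjustment of clinical outcomes appears once, as a response to imbalance in co-interventions: "exploratory sensitivity analyses or covariate-adjusted analyses may be performed as appropriate".
- **Neuroimaging data analysis:** the only covariate named anywhere is age, and only for imaging: "age will be considered as a covariate in exploratory neuroimaging analyses where appropriate".
- **Sample size calculation:** an unadjusted two-sample t-test with difference 4.84, common SD 5.22, two-sided 5% level and 90% power gives 26 per group, raised to 62 in total for 15% dropout.

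**The concern.** The primary outcome is the BI gain over a fixed 14-day course. A patient in the first weeks after stroke and one in the sixth month are both eligible. If their expected gains over two weeks differ, time since stroke adds spread to the outcome that has nothing to do with treatment. An unadjusted test leaves that spread in the error term, although the variable that could remove it is already recorded. Subtracting the baseline score does not remove it, because two patients with the same starting BI can be at different stages of recovery.

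Two things are at stake. The interval around the treatment difference may be wider than it needs to be in a small trial. And if one arm happens to receive more early patients, nothing in the stated primary analysis takes account of it.

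**Working it through.** **1. The plan's own figure.** The formula in the article gives n = 2 × (1.960 + 1.282)² × 5.22² / 4.84² = 24.4, or 25 per group. The named t-test procedure uses the noncentral t distribution: power is 0.895 at 25 per group and 0.906 at 26. Dropout: 52 / 0.85 = 61.2, rounded up to 62. The stated 26, 52 and 62 all reproduce.

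**2. Inputs the document does not give.** Let D be the early-minus-late difference in mean 14-day BI gain and p the share of early patients. Both are assumptions. The article also does not say how long after stroke the pilot patients behind the 5.22 were treated. So two readings of 5.22 are needed.

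**3. Reading A: 5.22 is the SD within a recovery phase.** Total SD = √(5.22² + p(1 − p)D²). With p = 0.5 and 26 per arm:

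| D | Total SD | Unadjusted power |
|---|---|---|
| 0 | 5.22 | 0.906 |
| 3 | √(27.25 + 2.25) = 5.43 | 0.88 |
| 5 | √(27.25 + 6.25) = 5.79 | 0.84 |
| 10 | √(27.25 + 25) = 7.23 | 0.66 |

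An even mix is the least favourable. With p = 0.8, power is 0.87 for D = 5 and 0.74 for D = 10.

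**4. Reading B: 5.22 already contains the phase spread.** The unadjusted power is the planned 0.906. Within-phase SD = √(5.22² − p(1 − p)D²). With p = 0.5:

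| D | Within-phase SD | Power with phase in the model |
|---|---|---|
| 3 | √(27.25 − 2.25) = 5.00 | 0.93 |
| 5 | √(27.25 − 6.25) = 4.58 | 0.96 |

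On this reading and an even mix, D cannot exceed 2 × 5.22 = 10.44, and D = 10 would leave a within-phase SD of only 1.5. Large values of D are therefore not credible here.

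**5. Bias and type I error.** In simulation (10,000 runs per setting, 26 per arm, p = 0.5, D from 0 to 15), the unadjusted type I error was 0.048 to 0.053. The mean unadjusted estimate was 4.82 to 4.87 for a true 4.84. With phase in the model, power under Reading A stayed at about 0.90 for every D.

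**6. Chance imbalance is the same variance seen from another side.** For D = 5 at 26 per arm, the within-phase standard error is 5.22 × √(2/26) = 1.448. The SD of the shift due to imbalance is 5 × √(2 × 0.25/26) = 0.693. Together, √(1.448² + 0.693²) = 1.605, which is exactly 5.79 × √(2/26). The shift is already inside the inflated SD and must not be added to it. For a single realised trial: with unrestricted assignment, 31 per arm and p = 0.5, the early share differs between arms by 20 percentage points or more with probability about 10%. That moves the estimate by 0.2 × D, which is 1.0 point for D = 5 or 2.0 for D = 10, against a target of 4.84.

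**The case against.** The strongest reply is that nothing is invalid. Allocation is randomised and concealed, so chance imbalance is already covered by the test and its interval. **This stands.** A reader might infer from the wide window that the primary result will be distorted, or that natural recovery will pass for a treatment effect. The document does not support that: over repeated trials the unadjusted comparison is unbiased and holds its error rate.

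Second, the article nowhere says that BI gain depends on time since stroke, or by how much, and the pilot SD may already include that spread. **This stands too.** It rules out quoting any single power loss as a fact. The low figures belong to Reading A with an even mix and a large D.

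Third, the recovery of power to about 0.90 in the simulation is partly built in, because the model adjusts for exactly the variable that generated the data. Real gains from an imperfectly chosen form would be smaller. **Accepted.**

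Fourth, a broad window suits a pragmatic trial, and an article commonly leaves covariates and stratification factors to the full protocol or analysis plan. **This stands in part.** The window is a legitimate choice, and silence about stratification does not prove there is none. But the article is not merely silent on the comparison: it names an unadjusted test, sizes the trial on one, and mentions adjustment of clinical outcomes only as an option tied to co-intervention imbalance. The point addresses that stated choice.

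**Conclusion.** The point holds as one of efficiency. The stated primary comparison leaves out, as covariates, two variables the trial already records: baseline BI and time since stroke. Its validity is not in question.

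The size of the loss is conditional. With an even early/late mix and 5.22 as a within-phase SD, power at 26 per arm is about 0.88, 0.84 or 0.66 for D = 3, 5 or 10. If 5.22 already covers the phase spread, the planned 0.906 stands, and adjustment raises it to about 0.93 or 0.96 for D = 3 or 5. If D is near zero, adjustment changes almost nothing. None of D, the mix or the make-up of the pilot group is given, so the document cannot say which case applies. In each of these cases adjustment either helps or costs very little. The calculations concern time since stroke only; any gain from baseline BI comes on top and has not been quantified.

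**What to change.** Before unblinding, state the primary analysis as an ANCOVA of post-treatment BI on treatment group, baseline BI and time since stroke. Fix one form of the last variable in advance, for example log days since onset, so that no choice is left for after the data are seen. Use the same time-since-stroke covariate in the models for the NIHSS and the mRS. Keep the unadjusted comparison as a supporting analysis if wanted.

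It would also help to report how long after stroke the pilot patients behind the 5.22 were treated, since that decides which reading of the power applies.

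The cost is a change of analysis wording and about one degree of freedom per covariate. No new data are needed and the entry window can stay. Stratifying the allocation list by time since stroke is optional, and only worth considering if the list can still be changed.
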